### Intervention

Standard treatment (ST) arm

Participants will receive a brief smoking cessation intervention based on the ‘5A’ and ‘5R’ models proposed by the World Health Organization. The ‘5A’ model emphasizes five steps: ***A***sking about tobacco use, ***A***dvising smokers to quit, ***A***ssessing their willingness to quit, ***A***ssisting in quitting, and ***A***rranging for follow-up [8]. Accordingly, our trained research assistant (RA) will ask participants about their tobacco use. The RA will then advise them to quit by a strong message: ‘*According to the World Health Organization*, *smoking kills one in every two smokers*. *Quitting smoking is important to protect your health*. *We are here to help you*.*’* The RA will then assess their willingness to quit by asking two questions: *‘Would you like to quit smoking*?*’* and *‘Do you think you can quit smoking successfully*?*’* If the participant replies *‘yes’* to the first question and either *‘yes’* or *‘unsure’* to the second question, they will be considered smokers who are ready to quit, and the RA will assist them to quit using the **STAR** method: ***S***et a quit date within 1 week, ***T***ell people around them about the participant quitting and solicit support, ***A***nticipate challenges to quit attempt, and ***R***emove all tobacco products. Participants who reply either *‘unsure’* or *‘no’* to the first question and *‘no’* to the second question will be considered smokers who are not yet ready to quit and the ‘5R’ model will be applied. This model comprises five components: ***R***elevance, ***R***isks, ***R***ewards, ***R***oadblocks and ***R***epetition. Accordingly, the RA will ask participants to think about how quitting smoking is personally relevant and encourage them to identify the potential risks of smoking and potential rewards of quitting. The RA will then guide participants to think about any roadblocks to quitting and provide corresponding solutions. Finally, the RA will repeat the assessment of their willingness to quit. Lastly, the RA will arrange follow-up with the participants by phone.

Booster intervention

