#### Integrated Intervention (II) arm

In addition to the brief smoking cessation intervention based on the ‘5A’ and ‘5R’ models, participants will receive brief advice on alcohol use based on the **FRAMES** model, which is a well-established and effective brief intervention for drinking [28]. The acronym is defined as ***F***eedback of personal risk for alcohol use, emphasis on personal ***R***esponsibility for change, clear ***A***dvice to change, ***M***enu of alternative options, ***E***mpathy as a counseling style, and enhancing self-***E***fficacy.

The RA will invite participants to complete the Alcohol Use Disorders Identification Test (AUDIT) and provide personalized feedback accordingly. AUDIT is a simple instrument that was developed by the World Health Organization to identify individuals who are hazardous drinkers or have active alcohol use disorders. In Hong Kong, there is currently no recommended level of alcohol use because the harmful effects of drinking are considered to outweigh any potential health benefits [29]. A longitudinal study of population cohorts from 1990–2016 across 195 countries and territories also concluded that there is no safe level of alcohol consumption [30]. Therefore, the RA will advise participants to achieve zero alcohol consumption, provided they are classified to have low risk according to the AUDIT (scoring 1–7). After providing the personalized feedback stipulated in AUDIT, the RA will emphasize personal responsibility for change by advising, *‘No one can make this choice for you*. *It is really up to you to make a change*.*’* Additionally, the RA will advise participants, ‘*As a trained counsellor*, *I strongly advise you to stop drinking*. *This can benefit your health and increase your chance of smoking abstinence*.*’* If participants agree to stop drinking, the RA will assist them in identifying five strategies for change, e.g. alternating alcoholic drinks with soft drinks. Throughout the process, the RA will establish an empathetic relationship with participants. Moreover, the RA will support participants’ self-efficacy by saying, *‘Many people can successfully stop drinking*. *With appropriate information and our support*, *I am sure that you can do it as well*.*’* The brief advice on alcohol use will take ≤15 minutes to avoid significantly lengthening the intervention [28].

Booster intervention

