### Outcome

The primary outcomes are feasibility measures: screening rate, eligibility rate, consent rate, randomization rate, attendance rate of intervention, adherence to intervention protocol, retention rate, completion rate, missing data, and adverse events. The secondary outcomes are effect size of II on self-reported and biochemically validated quit rates at 6 months relative to control and ST. These quit rates are the most useful outcomes to show the effectiveness of smoking cessation interventions [21]. Six months was chosen because it is the gold standard follow-up duration for evaluation in smoking cessation trials [4,15–20,31].

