### Measurements

Feasibility measures include screening rate (the number of eligible smokers divided by the number of screened people), eligibility rate (the number of eligible smokers divided by the number of screened people), consent rate (the number of eligible smokers who agree to participate divided by the number of eligible smokers), randomization rate (the number of participants who are randomized divided by the number of eligible smokers who consent to participate), attendance rate(the number of participants who complete the intervention divided by the number of participants who are randomized into the treatment arms (ST and II)), adherence to intervention (the number of participants in the two treatment arms who practice the skills learned during the intervention divided by the number of participants in the two treatment arms), retention rate (the number of participants who remain in the study divided by the number of participants randomized), completion rate (the number of participants who complete the questionnaire divided by the number of questionnaires distributed), missing data (the percentage of missing data), and adverse events (unfavorable or unintended events during the study period that were not present at baseline or appear to have worsened since baseline [32]).

The proposed secondary trial outcome is effect size of II on self-reported and biochemically validated quit rates at 6 months relative to control and ST. The self-reported quit rate will be measured using a structured questionnaire designed by our team. The questionnaire will cover six areas: smoking profile (i.e., number of cigarettes smoked per day, age when starting to smoke, years of smoking, and the Fagerstrom test, which is the gold standard test for physical dependence on nicotine) [15–20,31], cessation history (i.e., previous quit attempts, when previous quit attempt was initiated, and duration of abstinence), readiness to quit, self-efficacy to quit, alcohol use, and demographics. Besides the items measuring the fact of participants, which are not possible to have the psychometric properties, the construct reliability coefficient for the Fagerstom test was 0.74 [33]. and the Cronbach’s alpha for measuring alcohol use using the Alcohol Abstinence Self-Efficacy Scale (AASE) was 0.98 [34]. The biochemically validated quit rate will be confirmed by measuring the level of carbon monoxide in expired air (< 4 ppm) and level of cotinine in saliva (< 115 ng/mL) [15–20,31].

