### Data collection

Participants will be recruited from smoking hotspots in Mong Kok. Smoking hotspots are places where many smokers congregate [31]. Mong Kok is one of the most popular places among Hong Kong youth, including young smokers [35]. The RA will approach smokers who smoke in selected smoking hotspots to deliver leaflets containing information of the study. If smokers are willing to participate, the RA will check their eligibility. Eligible smokers will be invited to join. For smokers who are ineligible or refuse participation, the RA will remind them of the health effects of smoking and drinking and refer them to the government’s quit line. The timeline of this study was presented in S2 File.

Data will be collected at baseline, 1 week, 1 month, 3 months, and 6 months, which are data collection timepoints that are commonly used in smoking cessation trials [4,19,20,31]. All participants will complete a structured questionnaire at each timepoints via telephone. Self-reported quitters at 6 months will be invited for biochemical validation.

Participants in the II arm with high (80%–100%) and low (0%–20%) adherence will be purposively selected for one-to-one, 20–30 minutes, semi-structured interviews to further assess the feasibility of II. All interviews will be conducted by the RA in a meeting room of a local university following a semi-structured interview guide and will be audio recorded. Sample size will be determined by data saturation. Based on previous smoking cessation studies [4,16], we expect data saturation to occur after interviewing 30 participants: 15 from the high adherence group and 15 from the low adherence group. As one outcome of this study is to test the feasibility of the II, no incentive will be provided to the participants.

The audit will be conducted by one auditor who was blinded to experimental or control sites. She will regularly audit the overall quality and completeness of the data, examine source documents, interview investigators and coordinators, and confirm that the clinical center has complied with the requirements of the protocol.

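### The single adherence rate, pooled over ST and II, cannot show whether the alcohol component of II was followed

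*Protocol article*

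**What the plan says.** The Outcome section makes adherence a primary measure: "The primary outcomes are feasibility measures: screening rate, eligibility rate, consent rate, randomization rate, attendance rate of intervention, adherence to intervention protocol", with four further measures after it. The Measurements section then gives a complete formula: "the number of participants in the two treatment arms who practice the skills learned during the intervention divided by the number of participants in the" same arms. It is one yes/no count over ST and II combined, with no split by arm or by component.

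The intervention sections show that some skills are given conditionally. For participants who want to quit and do not rule out success, "they will be considered smokers who are ready to quit, and the RA will assist them to quit using the" STAR method. Others "will be considered smokers who are not yet ready to quit" and receive the 5R discussion, which includes solutions to the roadblocks they name. II adds alcohol advice to the same smoking intervention, and there "If participants agree to stop drinking, the RA will assist them in identifying five strategies for change". At the four boosters, anyone still smoking (and, in II, anyone still drinking) gets brief suggestions, whatever they decided earlier.

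Under Data collection, adherence is used a second time: "Participants in the II arm with high (80%–100%) and low (0%–20%) adherence will be purposively selected" for interviews, with 15 expected from each group. Under Data analysis, the feasibility of II is the first objective and rests mainly on the quantitative measures.

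**The concern.** The trial's first question is whether II is feasible. Its smoking part is the brief 5A/5R intervention, which the article itself describes as standard practice. The untested element is the alcohol advice, and the formula does not isolate it.

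Two features cause this. First, ST participants count in full although they have no alcohol component to follow. Second, an II participant who uses the smoking skills and ignores the alcohol strategies may or may not count, depending on how the wording is read. A reassuring value could therefore coexist with an unused alcohol component, and a poor value could come from ST alone. The Discussion says that a full-scale trial will be based on these results, so the planners would lack the adherence figure they most need.

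A lesser issue is that eligibility requires only one cigarette and one alcoholic drink in the past 30 days. Neither readiness to quit nor willingness to stop drinking is needed, so the rate mixes willingness to change with use of what was taught.

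**Working it through.** The plan states no expected adherence figure, so there is none to reproduce. The planned arm size of 50 comes from the Sample section. All practice and readiness rates below are assumptions, used only to show how the formula behaves.

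**Step 1: weight of each arm.** Rate = (ST adherers + II adherers) / (50 + 50). ST supplies 50/100 = half of the denominator. A reported 50% fits 50 of 50 in ST with 0 of 50 in II, and equally the reverse. The pooled figure alone does not fix adherence in II.

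**Step 2: components within II.** Let a share s of each arm use smoking skills, and let nobody in II use an alcohol strategy.

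- If any skill counts: (50s + 50s)/100 = s.
- If II participants must use both kinds: (50s + 0)/100 = s/2.

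| s | Any skill counts | Both required in II | Alcohol strategies used in II |
|---|---|---|---|
| 40% | 40% | 20% | 0% |
| 60% | 60% | 30% | 0% |
| 80% | 80% | 40% | 0% |

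The wording permits both readings. The same data give a twofold difference, and neither column shows that alcohol use of the strategies is zero.

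**Step 3: conditional delivery.** Let r be the share given the action skills, p the share practising among them, and q the share of the others who count as practising something learned from 5R or the boosters. Then rate = r × p + (1 − r) × q.

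Take p = 80%. At the extreme q = 0:

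- r = 70%: 0.7 × 0.8 = 56%
- r = 50%: 0.5 × 0.8 = 40%
- r = 30%: 0.3 × 0.8 = 24%

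If instead q = p, the rate is 80% whatever r is. At r = 50% the result thus lies between 40% and 80%, depending on how far 5R and booster content counts as a skill. Readiness can pull the rate down, but the documents do not fix by how much.

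**Step 4: the two uses of adherence.** The Measurements formula gives each person a yes or no and the group a percentage. The interview bands need a graded percentage for each II participant. The first cannot produce the second, and the article defines no other score.

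**The case against.** Several counter-arguments have force.

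- **Decliners are not left without content.** They get 5R with roadblock solutions, AUDIT feedback and advice in II, and booster suggestions over six months. A reader might infer that they were never taught anything and are scored non-adherent for that reason alone. The text does not support this; q = 0 in Step 3 is only an extreme.
- **An all-participants denominator is legitimate.** For feasibility it matters how many of those assigned end up using the skills, and this fits the intention-to-treat stance. A rate among the willing alone could flatter the intervention. The denominator is therefore not an error as such.
- **The any-skill reading is permitted, not stated.** It would be wrong to say that the plan counts smoking skills alone as adherence to II.
- **The interview bands are not the same score.** One might infer that people who declined the strategies would fill the low-adherence interview group. That needs the group proportion to be the participant-level score, which it cannot be.
- **Consequences are limited.** Adherence is one of ten descriptive measures, no progression threshold depends on it, and interviews supplement it. Alcohol use is also recorded, although drinking status is a behavioural outcome and not use of the strategies.

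The argument that a journal article condenses such detail succeeds only in part. Thresholds and time points may well be set elsewhere. The pooled numerator and denominator, however, are stated here in full, and it is that stated measure which does not answer the question about II.

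**Conclusion.** The point holds in a limited form. As written, the primary adherence measure cannot show whether II participants followed the alcohol component, because it pools ST with II and does not separate the skills within II. This follows from the text and needs no assumed rates. Its possible size does rest on assumptions: with 40% to 80% using smoking skills, the pooled rate could read 40% to 80% with no alcohol strategy used if any skill counts, or half of that if both kinds are required in II.

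That the rate partly reflects willingness to change is a secondary point of unknown size. The yes/no count and the graded interview bands also need to be reconciled. No efficacy or safety conclusion depends on this, but a primary feasibility measure does, and which components were delivered to whom is hard to reconstruct afterwards.

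**What to change.** 1. In Measurements, replace the pooled ratio with adherence by arm and component: smoking skills in ST, smoking skills in II, and alcohol strategies in II only. Keep everyone randomized to the arm as the main denominator.
2. Record at each session who was given the STAR steps and the five drinking strategies. As supporting figures, show uptake (given / randomized) and practice among those given.
3. Define the participant-level score behind the 80%–100% and 0%–20% bands and state how it relates to the yes/no count. Record whether each low-band interviewee had declined the strategies, and do not exclude those who had. Restricting the bands to people given strategies would be unworkable: if 50% to 70% of the 50 were given them, 25 to 35 people would remain for 30 planned interviews.

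The cost is one extra record per session and less precision. At a true rate of 50%, the approximate 95% half-width, 1.96 × √(0.25/n), is 9.8 points for the pooled 100 and 13.9 points for one arm of 50. For conditional figures based on 35 or 25 people it is 16.6 or 19.6 points.

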A literature search has identified some studies that investigated integrated interventions [10–13]. For example, one pilot study evaluated the acceptability of an integrated smoking cessation and drinking intervention in young adults [10]. A total of 41 young adult smokers who were regular drinkers were randomly assigned to either the standard treatment (eight individual-based counseling sessions plus 8 weeks of nicotine patch therapy) or integrated intervention. Results demonstrated that the integrated intervention was highly acceptable to young smokers. Furthermore, young smokers who received the integrated intervention reported higher biochemically validated quit rates than those who received the standard treatment. Another study was a two-arm randomized controlled trial (RCT) comparing the efficacy of a technology-based integrated smoking cessation and alcohol intervention and a smoking cessation only intervention in adolescents [11]. A total of 1471 participants were randomized into one of the interventions and results indicated that the integrated intervention exhibited no advantages of self-reported quit rates over the smoking cessation only intervention.

Although these studies addressed the effectiveness of integrated smoking cessation and alcohol interventions, they had limitations that warrant further investigation. The study by Ames et al. [10] did not use intention-to-treat to handle missing data, leading to an overestimation of the intervention effect. Despite promising findings, the results were not statistically significant because of an insufficient sample size. In the study by Haug et al. [11], participants’ smoking status was not biochemically verified, which may have led to an overestimation of intervention effectiveness because of social desirability bias. Moreover, the study did not have a control group, precluding conclusions regarding absolute intervention effectiveness. Third and perhaps most importantly, some participants did not have alcohol drinking and therefore, an integrated intervention is less relevant to these individuals, weakening the intervention effectiveness and contributing to the non-significant findings. Because of these limitations, re-examining the effectiveness of integrated smoking cessation and alcohol interventions in young smokers in a large-scale RCT is imperative. Our pilot study will be an important prerequisite to ensure feasibility of implementing such interventions in the Hong Kong Chinese context.

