### Sample

Individuals are eligible for the study if they are (1) aged 18 to 25 years, (2) smoked at least one cigarette in the past 30 days, (3) consumed at least one cup of alcohol (10 ounces of beer, 4 ounces of wine, or 1 ounce of liquor) [4] in the past 30 days, and (4) speak Cantonese. Exclusion criteria include: (1) have cognition and/or communication problems, (2) have clinically reported mental disorders (anxiety, depression, etc.), (3) current use of nicotine containing medication, (4) participating in other smoking cessation interventions including pharmacological interventions. We will target participants aged 18–25 years because this age range is considered young adulthood [22]. Smokers aged <18 may also have alcohol drinking; however, their psychosocial development differs from those who reach the age of majority [23]. Therefore, we only targeted those aged 18–25 years to ensure the homogeneity. As this study aims to explore the feasibility and preliminary effect of II on smoking cessation among young smokers, we do not set any restriction on nicotine dependency. Hence, light and heavy smokers will be included. This variable will also be controlled in our GEE model. However, non-smokers will not be included. Similarly, we will not set any restriction on the participants’ alcohol dependency. However, participants will be categorized as heavy drinkers when exceeding the following threshold: drinking on a maximum of 5 days per week, maximum 3 glasses per day and 14 per week for women, and maximum five glasses per day and 21 per week for men [24]. This variable will also be controlled in the GEE model. According to Department of Health, Hong Kong [25], regular drinkers are defined as those who drink at least once in 7 days, whereas occasional drinkers are those who drink once in 30 days. We will include occasional drinkers because occasional drinking can also lead to smoking lapses and relapses [4].

There is no fixed rule for calculating sample size for a pilot study [26]. Based on the sample size estimation guide for pilot studies outlined by Birkett and Day [27]. 50 participants per arm will provide 80% power to detect differences between the groups, assuming a 5% alpha error and a 10% attrition rate. Hence, a total of 150 participants will be recruited for this study.

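### For the light smokers this trial enrols on purpose, a saliva cotinine cut-off of 115 ng/mL adds little, so validation of a quit rests almost entirely on expired CO

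*Protocol article*

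**What the plan says.** Under Measurements, a quit is biochemically validated by "measuring the level of carbon monoxide in expired air (< 4 ppm) and level of cotinine in saliva (< 115 ng/mL"). Both conditions apply, with the same limits for every participant.

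Under Sample, the smoking criterion for entry is having "smoked at least one cigarette in the past 30 days". No limit is set on nicotine dependency: "Hence, light and heavy smokers will be included". People with "current use of nicotine containing medication" are excluded at entry.

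Under Data collection, questionnaires are completed by telephone, and then "Self-reported quitters at 6 months will be invited for biochemical validation". No interval between the call and the test is given.

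Under Outcome, "The secondary outcomes are effect size of II on self-reported and biochemically validated quit rates at 6 months relative to control and ST". The primary outcomes are feasibility measures. The Discussion says that a full-scale trial will be based on the results.

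The Introduction criticises an earlier trial because "smoking status was not biochemically verified, which may have led to an overestimation of intervention effectiveness because of social desirability bias".

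**The concern.** The two markers do different jobs. CO shows whether someone smoked recently, and cotinine is the longer-lived marker that should cover the gap before that. A cotinine limit can do so only if a continuing smoker would exceed it. One limit of 115 ng/mL applied to a sample that deliberately reaches down to one cigarette a month raises the question of whether the lighter participants could ever exceed it.

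The issue is not confined to those who enter as light smokers. The sample reflects consumption at 6 months, so a heavier smoker who has cut down to a few cigarettes a day and reports having quit is in the same position.

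At stake is how far the validated quit rate improves on self-report in this group. By the protocol's own reasoning, that improvement is the purpose of verification. The result feeds a secondary effect size that is meant to inform a larger trial.

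**Working it through.** **The plan's own figure.** The 115 ng/mL limit is given with citations and without a derivation, so there is nothing to reproduce. The article gives no cotinine level by smoking rate, no definition of a light smoker and no timing of the CO test relative to the last cigarette. The inputs below that do not come from the document are assumptions, shown with ranges.

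**Step 1: cotinine yield per cigarette per day (assumed).** Yield = nicotine dose × 0.72 × (176.2/162.2) ÷ clearance × saliva:plasma ratio.
- Low: 0.5 mg, 80 L/day, ratio 1.0: 0.5 × 0.72 × 1.086 ÷ 80 = 0.0049 mg/L, about 5 ng/mL.
- High: 1.5 mg, 50 L/day, ratio 1.25: 1.5 × 0.72 × 1.086 ÷ 50 × 1.25 = 0.0293 mg/L, about 29 ng/mL.

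**Step 2: who passes the cotinine limit.** Level = yield × cigarettes per day.

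| Current smoking | Level at yields 5 to 29 (ng/mL) | Below 115? |
|---|---|---|
| 1 per 30 days (entry floor) | 0.17 to 0.97 | always |
| 1 per day | 5 to 29 | always |
| 3 per day | 15 to 87 | always |
| 5 per day | 25 to 145 | unless yield is 23 or more |
| 10 per day | 50 to 290 | unless yield is 11.5 or more |

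The consumption at which 115 is reached is 115 ÷ yield: 23.0, 11.5, 7.7, 5.8 and 4.0 cigarettes a day at yields of 5, 10, 15, 20 and 29. At the entry floor, reaching 115 would need a yield of 115 × 30 = 3450, so the result there does not depend on the assumption.

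**Step 3: what CO can add.** Time to fall below 4 ppm = half-life × log2((start − background) ÷ (4 − background)). With an assumed start of 8 ppm and background of 1.5 ppm, log2(6.5 ÷ 2.5) = 1.38, which gives 2.8, 5.5 and 8.3 hours for half-lives of 2, 4 and 6 hours. Over wider assumptions (start 5 to 20 ppm, background 0 to 2 ppm, half-life 2 to 8 hours) the range is about 0.6 to 25 hours. CO can catch someone who smoked shortly before the test. It will not catch someone who smokes every few days.

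**Step 4: effect on the comparison (illustrations only).**
- *Equal false reporting.* True quit rates 5% and 15% (OR 3.35), with 10% of continuing smokers in each arm falsely reporting a quit. Validated rate = p + (1 − p) × 0.10 × (1 − detection). Joint detection of 0%, 30%, 60% and 90% gives ORs of 1.81, 2.01, 2.34 and 2.98. Both rates rise and the effect shrinks.
- *Unequal false reporting.* True rate 10% in both arms, with false reports from 5% of control and 10% of II non-quitters, and only those of light smokers passing. Validated rate = 0.10 + 0.90 × false-report rate × light share. Light shares of 30%, 50% and 70% give 11.4% v 12.7%, 12.3% v 14.5% and 13.2% v 16.3%, with spurious ORs of 1.14, 1.21 and 1.29. The unrounded excess is 1.35 to 3.15 percentage points, about 0.7 to 1.6 participants out of 50.

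**Step 5: what a lower cut-off would catch.** At 10 ng/mL the detectable consumption is 10 ÷ 29 to 10 ÷ 5, or 0.3 to 2 cigarettes a day. At 20 ng/mL it is 0.7 to 4 a day. Neither detects a person at the entry floor.

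**The case against.** The strongest reply is that both conditions must be met. A daily light smoker who smoked shortly before the test can fail on CO, so a false report can be refuted. That stands. A reader might infer that the validated rate cannot refute any false report from a light smoker, but the sentence that sets the cotinine limit also sets the CO limit and rules that reading out. Nor does the document say how much notice participants have. Notice is implied by a telephone report followed by an invitation, but no interval is stated.

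A reader might also infer that the flaw inflates II against control. Blinding is ruled out, and II and ST are praised for stopping while control hears about fruit and vegetables, so unequal false reporting is plausible. Nothing in the document quantifies it, however. Control also receives a cessation leaflet and contacts of the same duration, and equal false reporting moves the effect the other way. For II against ST the smoking advice is the same, which gives even less basis for a direction. The second illustration further assumes that CO detects none of the light smokers' false reports and that everyone invited attends.

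It is also fair to say that the yield is assumed, that smokers of 5 a day exceed 115 ng/mL at the top of the assumed range, and that the citations behind the limit were not available for this check. These points limit how far up the smoking range the problem extends. They leave the result for about 3 cigarettes a day and below untouched.

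Finally, the distortion is small beside the sampling error of this pilot. At a quit rate near 12% with 50 per arm, the 95% interval for a difference is about ±1.96 × √(2 × 0.12 × 0.88 ÷ 50), or ±13 points. Sensitivity analyses and subgroup tables are often left to an analysis plan, which is not shown here. The threshold itself, though, is fixed in this article.

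**Conclusion.** The point holds in a limited form. For people smoking up to about 3 cigarettes a day, the cotinine limit is passed across the whole assumed range of 5 to 29 ng/mL per cigarette per day. At mid-range yields of 10 to 20, it is passed up to about 5 to 11 a day. For light, intermittent or cut-down smokers, validation is therefore close to a CO test alone, and some of the social desirability bias that the protocol criticises elsewhere can remain.

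The size and direction of the resulting error cannot be fixed from the document. They depend on the share of light smokers, the rate of false reporting in each arm, and the timing of the CO test. Only the secondary effect size is affected, and the primary feasibility outcomes are not. The change is worth making because it is cheap and because the effect size is meant to inform a larger trial. The document does not support replacing the 115 ng/mL definition outright.

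**What to change.** In Measurements, keep the CO reading and the saliva sample as planned and add the following.

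1. Record the numeric cotinine value, or the lower band if a strip is used.
2. Prespecify, before any data are seen by arm, a second definition of a validated quit: CO < 4 ppm and a lower cotinine cut-off chosen for light smokers. On the assumed yield this is about 10 to 20 ng/mL, and it should not be below the assay's limit. The sponsor should justify the value chosen.
3. Report this beside the < 115 ng/mL definition, and tabulate both by baseline cigarettes per day, which the questionnaire already collects.

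The cost is a few lines of text and one further analysis of samples already planned, with no new visit or participant. The validated rate under the second definition will be somewhat lower, and true quitters with other nicotine exposure may fail it, since nicotine medication is excluded only at entry. Showing the < 115 ng/mL result alongside makes that visible. Very infrequent smokers would remain undetected, and the report should say so.
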